## Abstract

**Introduction:**

The optimal preoperative preparation for elective colorectal cancer surgery has been debated in academic circles for decades. Previously, several expert teams have conducted studies on whether preoperative mechanical bowel preparation and oral antibiotics can effectively reduce the incidence of postoperative complications, such as surgical site infections and anastomotic leakage. Most of the results of these studies have suggested that preoperative mechanical bowel preparation for elective colon surgery has no significant effect on the occurrence of surgical site infections and anastomotic leakage.

**Methods/design:**

This study will examine whether oral antibiotic bowel preparation (OABP) influences the incidence of anastomotic leakage after surgery in a prospective, multicentre, randomized controlled trial that will enrol 1500 patients who require colon surgery. The primary endpoint, incidence of anastomotic leakage, is based on 2.3% in the OABP ± mechanical bowel preparation (MBP) group in the study by Morris et al. Patients will be randomized (1:1) into two groups: the test group will be given antibiotics (both neomycin 1 g and metronidazole 0.9 g) the day before surgery, and the control group will not receive any special intestinal preparation before surgery, including oral antibiotics or mechanical intestinal preparation. All study-related clinical data, such as general patient information, past medical history, laboratory examination, imaging results, and surgery details, will be recorded before surgery and during the time of hospitalization. The occurrence of postoperative fistulas, including anastomotic leakage, will be recorded as the main severe postoperative adverse event and will represent the primary endpoint.

**Ethics and dissemination:**

Ethics approval was obtained from the Chinese Ethics Committee of Registering Clinical Trials (ChiECRCT20200173). The results of this study will be disseminated at several research conferences and as published articles in peer-reviewed journals. Protocol was revised on November 22, 2021, version 4.0.

**Trial registration:**

ChiCTR2000035550. Registered on 13 Aug 2020.

**Supplementary Information:**

The online version contains supplementary material available at 10.1186/s13063-022-06235-7.

## Introduction

Preoperative preparation of elective colorectal surgery has been debated in academic circles for decades. In 1973, Nichols et al. conducted a prospective randomized controlled trial of preoperative mechanical bowel preparation (MBP) versus MBP + oral antibiotic bowel preparation (OABP) and published a subsequent retrospective analysis [1, 2]. The results showed that the combined treatment programme can significantly reduce incidence of postoperative complications. Since then, MBP and OABP have become part of preoperative preparation. Over the years, many expert teams have conducted various studies on whether preoperative mechanical bowel preparation and preoperative oral antibiotics can effectively reduce the incidence of postoperative complications, such as surgical site infections and anastomotic leakage. Most of the results of these studies have suggested that preoperative mechanical bowel preparation for elective colon surgery has no significant effect on the occurrence of surgical site infections and anastomotic leakage. On the other hand, preoperative oral antibiotics can effectively reduce the incidence of postoperative complications. Some studies [1, 3, 4] showed no benefit of MBP in open colorectal surgery. Cannon et al. [5] retrospectively studied 9940 patients undergoing colorectal resection from 2005 to 2009 and concluded that preoperative oral antibiotics should be used as part of preoperative preparation for elective colorectal cancer surgery, while the use of preoperative oral antibiotics alone should be validated in randomized trials. A retrospective study conducted in 2017 [6] analysed data from adult patients undergoing elective colorectal surgery between 2012 and 2014 through the NSQIP and concluded that OABP alone could effectively reduce the incidence of postoperative complications. In 2019, B Vadhwana et al. [7] conducted a prospective single-centre randomized controlled study (RCT) to compare the prognostic effects of MBP and MBP + OABP in patients undergoing elective colorectal surgery. They concluded that the preoperative strategy of MBP + OABP could significantly reduce the incidence of postoperative complications and accelerate the recovery of patients. The American Association of Colorectal Surgeons guidelines for bowel preparation in elective bowel surgery published in January 2019 also mentioned that the use of preoperative oral antibiotics alone is a low-grade recommendation based on low-quality evidence that still needs to be validated in randomized trials [8].

Currently, WHO guidelines do not recommend either preoperative oral antibiotics or mechanical bowel preparation alone but require a combination of mechanical bowel preparation and oral antibiotics for elective colon surgery [9]. UK NICE has suggested that preoperative mechanical bowel preparation should not be a part of routine preoperative preparation [10]. In an online survey of surgeons, the European Colorectal Society reported that more than 60% of colorectal surgeries in Europe involve mechanical bowel preparation before surgery, while only 11% of surgeons give patients oral antibiotics before surgery [11]. This situation is quite different from the trends of other domestic and foreign studies mentioned above. At the same time, Chinese research on the correlation between preoperative oral antibiotics and the incidence of postoperative complications is still in its infancy.

To date, there remains a lack of large-sample, multicentre, randomized controlled trial studies on the effect of oral antibiotics before colorectal surgery on the incidence of postoperative anastomotic leakage in the international colorectal treatment field to establish relevant norms for preoperative preparation. Therefore, the aim of this multicentre, pragmatic, adaptive, large-sample RCT is to prove that oral antibiotics alone, compared with no bowel preparation, could effectively reduce postoperative surgical site infection, anastomotic leakage, and hospital readmission in patients undergoing elective colorectal surgery.

## Methods/design

The protocol was structured following the Standard Protocol Items: Recommendations for Interventional Trials (SPIRIT 2013 Checklist) [12] (Appendix S1). The study protocol can be accessed at the chictr.org.cn website (ChiCTR2000035550).

### Study design

This study is a large-sample, multicentre, Superiority RCT in which 1500 patients were randomly assigned to the test group or the control group in a 1:1 allocation ratio. Figure 1 shows the trial flow chart.

**Fig. 1 Fig1:**
[figure not shown]
This is the whole flow diagram of the test

### Main objective

By grouping 1500 patients who need colorectal cancer surgery according to the process shown in Fig. 1, we will explore examined whether oral antibiotics alone before surgery could effectively reduce the incidence of anastomotic leakage after surgery.

### Inclusion and exclusion criteria

Patients who have been diagnosed with colorectal tumours and are considered for elective surgery (including partial and total resection, with conventional laparotomy and two- or three-hole laparoscopic surgery) and have no obvious contraindications to surgery are considered eligible for this study after the patients and their families agreed to voluntarily participate in the clinical trial and sign the relevant informed consent following a conversation regarding informed consent and the clinical trial.Patients meeting any of the following conditions will be excluded:
Patients who take various antibiotics on their own or under medical orders for various reasons within the 2 weeks before surgery;Patients with previous or present diagnosis of inflammatory bowel disease;Patients with a diagnosis of acute intestinal perforation or acute small intestinal diverticulum;Patients with ischaemic colitis or infectious colitis included in the diagnosis;Patients who require two or more operations at the same time;Patients who have been diagnosed with acute or chronic peritonitis or other infectious diseases requiring perioperative anti-infective treatment;Patients with any acute physiological disorder indicating that the patient needs emergency, rather than elective surgery [e.g., requires preoperative mechanical ventilation or there is preoperative acute renal failure, preoperative systemic inflammatory release syndrome, sepsis or septic shock, etc.);Patients with ASA grade 5;Patients with immunodeficiency, immunosuppression or autoimmune diseases (e.g., patients undergoing allogeneic bone marrow transplantation within the last 5 years, taking immunosuppressive drugs, diagnosed with SLE, etc.);Patients who refuse to sign informed consent to participate in the trial;Patients who are unable to cooperate in a normal fashion with the doctor due to personal reasons or other circumstances in which the investigator considers participation in the experiment unsuitable;Patients who require single-port laparoscopic procedures, natural-port procedures, and various new procedures;The terminating study criteria are as follows:
Patients who violate the principles of treatment after enrolment (e.g., violate the criteria for enrolment and discharge or do not comply with the medication or surgical arrangement for the study duration);Patients who were unable to undergo surgery for various reasons after enrolment (reasons will be recorded);Patients experiencing nonstudy-related complications such as drug allergies after enrolment;Patients who the investigator does not consider appropriate for continuation (reasons for withdrawal need will be documented);Patients who develop severe complications or unacceptable adverse reactions; andPatients who were unable to undergo elective surgery due to sudden aggravation or other reasons after enrolment.

### Recruitment

Recruitment will be encouraged by scheduled newsletters to participating centres. Participants will be given free treatment drugs, appointment registration and hospitalization in advance. Appropriate economic compensation, such as transportation subsidies will also be provided.

### Randomization/Assignment of interventions

Randomization was stratified by centre. Once informed consent is obtained, randomization will be performed via a centrally managed database. After receiving the patient grouping information, designated researchers at each centre will prepare trial drugs or placebo for patients according to the assigned group. In this process, only the researchers are informed about the grouping of patients. They will sign a confidentiality agreement and will not participate in any other links of the trial to ensure that they will not have any impact on the study. After collecting all the data, the designated researcher named the two groups A and B. The analyst will analyse the primary and secondary results without knowing the group name. Only after the analysis of the primary and secondary results can complete blindness be eliminated and ineffective blinding events recorded (for example, the study nurse discloses the patient’s specific medication to the doctor).

The nurses provided the patients with oral antibiotics for the experimental group and placebo for the control group in the ward.

### Allocation concealment mechanism

Randomization will be stratified in each centre. The randomization was performed on a centrally managed database once informed consent is obtained.

### Implementation

The sequence will be generated and forwarded by the computer specialist who created the case report form (CRF) online to implement the online database. By doing so, each centre/investigator can randomize their patients and assign them to the respective group of treatments. The date of randomization will be recorded.

### Blinding (masking)

The blind level was set as double-blind. All patients, doctors, data collectors and analysts will be unaware of the grouping of patients.

### Unblinding

If during the trial the subject has not developed a pregnancy or other emergency, Unblinding is performed in accordance with the normal procedure, i.e. after the trial is closed, checking the CRF against the signatures, a level I Unblinding is performed. The grouping of subjects was determined by Unblinding in level I for statistical analysis. Level II Unblinding was performed after statistical closure and statistical judgment had been made. Drug efficacy was evaluated by Unblinding level II to identify the test and control groups. In the event of an SAE, emergency Unblinding is generally not required and can only be performed if the study drug used has an impact on the choice of treatment regimen. Emergency Unblinding required the investigator to notify the study nurse prior to Unblinding, Unblinding based on the information provided by the study nurse about the medications taken by this subject. The investigator must indicate this on the CRF and complete the Unblinding record form.

### Treatment protocols

All eligible patients with colorectal cancer will be randomly assigned to the test group or the control group in a 1:1 allocation ratio. Participants in both groups will undergo similar perioperative procedures with the exception that the test group will receive oral antibiotics before surgery. For the test group, antibiotics will be given (both neomycin 1 g and metronidazole 0.9 g) the day before surgery (at 1 pm, 3 pm and 10 pm). The control group will take the same dose of placebo as the experimental group (Table 1). Intraoperative anal water injection experiments and infiltration by ICG fluorescence were performed to ensure the quality of the anastomosis.

**Table 1 Tab1:** The medication and usage in this experiment

		Time of drug administration		
Drug name	Dose	13:00	15:00	22:00
Neomycin/placebo	1 g			
Metronidazole/placebo	0.9 g			

### Permitted and prohibited related treatment and care

#### Preoperative management

Inclusion once eligibility has been achieved, surgery should be performed within 2 weeks (inclusive day 14).

After enrollment and until the expected surgical day, if clinical deterioration required the decision to undergo elective surgery as planned based on the judgment of the physician in charge; If emergency surgery was required or if surgery was cancelled, this screening case failed and was not enrolled.

Patients at nutritional risk were allowed preoperative implementation of enteral/parenteral nutrition support.

Perioperative low-molecular-weight heparin prophylaxis, lower extremity antithrombotic pants, aggressive lower extremity massage, and respiratory function training are recommended for high-risk patients who are of advanced age, have smoked, have diabetes mellitus, are obese, have a prior history of chronic cardiocerebral or thromboembolism, and so on. Methods for other potentially high-risk complications were not specified in the study protocol, and decisions were made by the physician in charge at each participating centre based on routine and specific needs of our centre’s clinical practice, but all nonconventional preoperative preparation measures were required to be documented in the CRF.

For patients with a preoperative smoking history, smoking cessation for 4 weeks before surgery is recommended. But this study is not mandated and smoking cessation status and time need to be recorded in the CRF.

For the surgical selection of the procedures performed in this study, the extent of abdominal lymph node dissection, and the method of digestive tract reconstruction were decided by the surgeon in charge of the procedure based on their experience and intraoperative specific circumstances.

Patients' preoperative fasting, water control and other pre-anaesthetic requirements were performed according to the anaesthetic routine protocol of each participating centre, which was not specified in this study.

#### Postoperative management

The observation endpoint was set as 30 days after surgery in this study, and no special requirements were made for postoperative analgesia, fluid replacement, and nutritional support.

### Clinical data

Clinical data from patients will be obtained by medical staff and recorded on an online electronic platform (Http://www.medresman.org.cn) and in the CRF table. The sample will be coded, and the patient’s identity will be known only by the attending physician. The clinical data will include the following: general patient information, past medical history, past surgical history, laboratory examination results, imaging results, surgery details, postoperative infection rate, incidence of postoperative complications, incidence of anastomotic leakage, and 30-day readmission rate after surgery. The timing and processing of the above-recorded contents will all be reflected in the CRF table, and the laboratory examinations will mainly assess preoperative and postoperative routine blood and inflammatory indicators (Table 2).

**Table 2 Tab2:** The test and data acquisition schedule for this experiment. Intraoperative anal water injection experiments and infiltration by ICG fluorescence were performed to ensure the quality of the anastomosis

Trial flow chart									
Stage		Preoperative		Intraoperative		Postoperative		Unplanned follow-up	
Follow up period	2–3 days	1 day	Intraoperative	1 day	3 days	5 days	14 days	30 days	Unplanned follow-up
Baseline data collected	√	—	—	—	—	—	—	—	—
inclusion and exclusion	√	—	—	—	—	—	—	—	—
Sign informed consent	√	—	—	—	—	—	—	—	—
Group determination	√	—	—	—	—	—	—	—	—
Fill in the basic information	√	—	—	—	—	—	—	—	—
Physical examination	√	—	—	—	—	—	—	—	—
Imaging examination	√	—	—	—	If necessary	If necessary	√	If necessary	If necessary
Blood routine examination	√	—	—	—	√	√	√	If necessary	If necessary
Oral antibiotics	—	√	—	—	—	—	—	—	If necessary
Safety observation	—	—	√	√	√	√	√	√	If necessary
Operational observation	—	—	√	—	—	—	—	—	If necessary
Record adverse events	—	—	√	√	√	√	√	√	If necessary
Other works	√	√	√	√	√	√	√	√	If necessary

A detailed description of the above data is shown in the CRF table.

### Sample size estimate

Due to the lack of international studies on the correlation between the use of oral antibiotics alone and the incidence of anastomotic stoma after surgery, we can only refer to the correlation data between oral antibiotics before surgery and the incidence of total complications in the previous literature to estimate the sample size. Based on the data in the study by Morris et al. [5], the anastomotic leakage rate in this trial was defined as 2.3%, and there is minimal literature available on the comparison between OABP alone versus no preparation. To verify whether OABP is effective in reducing the incidence of anastomotic leakage after colorectal surgery, we designed a superiority test with a superiority margin of 1% (*α*= 0.01, *β*= 0.01, 99% power). With a standard error of 0.01 and a confidence interval of 99%, a sample size of 1232 was needed. To minimize sampling error and account for the rate of loss to follow-up for various reasons, we determined the sample size to be 1500.

### Strategies to improve adherence to protocols

Screening: fill in the screening form before enrolment, and attach the gastroscopy, CT, and angiography data.Follow up: telephone/Internet follow-up is allowed. It is recommended that the researcher provide follow-up methods (telephone, micro signal, etc.) to the subjects.Withdrawal/protocol change: it is necessary to collect the reasons for withdrawal/protocol change and the treatment options after withdrawal/protocol change.

### Efficacy assessment indicators

The main efficacy indicator will be the percentage incidence of anastomotic leakage after surgery. Anastomotic leakage will be defined as the breakdown of the connection and subsequent leakage of digestive system fluid from a surgical anastomosis of digestive system structures. If postoperative anastomotic leakage is clinically suspected, digestive tract radiography will be performed to diagnose the leak. Usually, sufficient abdominal drainage is the most effective treatment.

The secondary efficacy indicators are postoperative recovery, as follows: (1) postoperative complications (*n*) at 30 days according to the Clavien–Dindo classification, which includes incisional infection, abdominal abscess, intraperitoneal haemorrhage, anastomotic bleeding, postoperative intestinal obstruction, pancreatitis, pulmonary complications, and other organ complications; (2) inflammation index at 1, 7, and 14 days after the operation; (3) rehospitalization rate within 30 days after operation (days); and (4) incision healing.

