### Harms

Adverse events refer to adverse medical events that occur in patients of this clinical trial after receiving the medications. In this study, an adverse event will be considered to the therapy from the time when patients sign the informed consent form to 1 month after the end of treatment. Assessing the nature and determining the severity of adverse events will be conducted in accordance with “expert consensus on diagnostic criteria for postoperative complications of gastrointestinal cancer in China”. To assess adverse events and their causal relationship to therapy, the investigator will evaluate the possible associations between adverse events and trial medications. The following five criteria will be used to determine the results: the time of occurrence of adverse events coincides with the time of administration, adverse events are related to known adverse reactions of the medication, adverse events cannot be explained by other reasons, adverse events disappear after discontinuing therapy and adverse events are reproduced after medication re-administration. The results documented as positive, relevant and possibly related will be deemed adverse reactions. The incidence of adverse reactions will be calculated accordingly. To record, process and report adverse events, the investigator will document any adverse events. Records of adverse events will include a description of adverse events and all related symptoms, time of occurrence, severity, duration, measures taken, the results and final outcomes. The reporting methods and treatment measures for severe adverse events will be classified as severe adverse events if they meet one or more of the following criteria: death, life-threatening (e.g., immediate risk of death), prolonged hospitalization or hospitalization, permanent or severe disability, congenital malformations or defects, some events that have not yet caused death, danger to life or hospitalization; we will also consider severe adverse events perpetrated by a physician if they cause harm to the patient or require medication or surgical treatment to avoid the above situation. For any severe adverse events during the clinical trial, the investigator will file a report of severe adverse events within 24 h and report in writing to the Ethics Committee, the superior authorities. The written report will include the time, severity, duration, measures taken and outcomes of serious adverse events.

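### Table 2 schedules no day 7 visit (and no routine bloods on day 1) for the inflammation endpoint, and no adverse event recording on the day the study drug is taken

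*Protocol article*

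**What the plan says.** **Inflammation endpoint.** In the protocol article, Efficacy assessment indicators, the second of the secondary indicators is "2) inflammation index at 1, 7, and 14 days after the operation". Under Clinical data, the article says that "the laboratory examinations will mainly assess preoperative and postoperative routine blood and inflammatory indicators (Table 2"), so Table 2 is where the reader is sent for the timing of these measurements. Its time row reads "Follow up period 2–3 days 1 day Intraoperative 1 day 3 days 5 days 14 days 30 days Unplanned follow-up", and its only laboratory row reads "Blood routine examination √ — — — √ √ √ If necessary If necessary".

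**Safety.** Under Treatment protocols, all study drug or placebo is taken "the day before surgery (at 1 pm, 3 pm and 10 pm"). Table 2 agrees: the oral antibiotics row has its only scheduled tick in the preoperative 1-day column. The rows "Record adverse events" and safety observation are both dashes in the two preoperative columns, and both are first ticked intraoperatively. The Harms section gives two starting points. It first describes adverse events as those arising once the medication has been received, and then sets the period as "from the time when patients sign the informed consent form to 1 month after the end of treatment". It also lists coincidence in time with administration among the criteria for causality, and plans to calculate an incidence of adverse reactions.

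**The concern.** A schedule of assessments is what site staff work from. If it disagrees with the endpoint definition, some centres will follow the table and others the text. The endpoint will then be missing, or measured on different days, according to centre. The inflammation index is a fixed-time endpoint, so a value from another day is not a substitute without a stated rule.

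The safety gap matters for a different reason. The intervention is three administrations on one day, and that is the day on which the table asks for no safety recording. Any reaction to the drug that starts before the operation falls in this interval. So do the events for which the causality criterion on timing is most informative.

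**Working it through.** No sample size, power or error rate is involved. The check is a cell-by-cell reading of Table 2 against the text.

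**Step 1: are the columns read correctly?** The time row has nine entries: two preoperative (2–3 days, 1 day), intraoperative, postoperative days 1, 3, 5, 14 and 30, and unplanned. The rows used here each have nine cells. The oral antibiotics tick falls under preoperative 1 day and the operational observation tick falls under intraoperative, as they should. The columns have not shifted in extraction.

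**Step 2: inflammation endpoint against scheduled bloods.**

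| Postoperative day | Endpoint text | Column in Table 2 | Routine blood row |
|---|---|---|---|
| 1 | yes | yes | dash |
| 3 | no | yes | tick |
| 5 | no | yes | tick |
| 7 | yes | none | none |
| 14 | yes | yes | tick |
| 30 | no | yes | if necessary |

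Endpoint days {1, 7, 14} and ticked days {3, 5, 14} share only {14}, so 1 of 3 agrees. The two mismatches differ in strength:

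- Day 7 has no column, so the mismatch holds however the laboratory row is read.
- Day 1 has a visit. The mismatch there depends on taking the row "Blood routine examination" as the place where inflammation markers are drawn. The Clinical data section supports that reading by referring both kinds of test to Table 2. Against it, the baseline list under Data collection and observation indicators names routine blood tests and the inflammation index as separate items. If they are separate, Table 2 has no row for the index on any day.

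**Step 3: safety rows against the dosing day.**

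| Column | Study drug | Adverse events | Safety observation |
|---|---|---|---|
| Preoperative 2–3 days | dash | dash | dash |
| Preoperative 1 day | tick | dash | dash |
| Intraoperative | dash | tick | tick |

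Recording is ticked in 0 of 2 preoperative columns. If the window opens at consent, which Table 2 places in the 2–3 day column, both dashes conflict with the Harms section. If it opens once medication has been received, only the dosing-day dash conflicts. The dosing-day cell is therefore inconsistent under either starting point. From the first dose at 13:00 to midnight is 24 − 13 = 11 hours, and the gap runs on until the operation, whose start time the article does not give.

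**Step 4: who could be lost?** The terminating criteria (under Inclusion and exclusion criteria) include drug allergy after enrolment and inability to undergo surgery. Preoperative management treats a cancelled or emergency operation as a screening failure. A patient who reacts to the drug and is not operated on never reaches the intraoperative column, the first one with a safety tick.

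**The case against.** The strongest reply is that Table 2 is a summary of visits in a condensed article. It refers to a CRF that is not shown, and its generic row for other works is ticked at every visit. The Harms section places a general duty on the investigator to document any adverse event, with its time of occurrence. A reaction on the dosing day can be entered at the intraoperative visit with its true onset time. Serious events are reported within 24 hours whatever the visit, and reasons for withdrawal are to be collected.

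Much of this stands, and it limits what can be claimed. Three stronger readings are tempting, and the documents do not support them:

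- A reader might infer that dosing-day events will not be recorded and that the adverse reaction incidence will be too low. The general duty to document means only that such events could be missed.
- A reader might infer that day 1 is certainly lost. That depends on reading the routine blood row as the inflammation row; only day 7 is firm.
- A reader might infer that the day 3 and day 5 results go unused. Nothing says so: the Follow-up section lists blood counts as follow-up tests in their own right.

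The reply does not remove the inconsistency. The article prints both the endpoint days and the schedule, and they disagree. A fuller CRF may add detail, but it cannot make the two printed statements agree. An unplanned visit held only if needed cannot supply a fixed-time value for every patient. The retrospective route for adverse events fails for a patient who never reaches the operating room.

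**Conclusion.** The point holds as two schedule inconsistencies that should be corrected. For the inflammation endpoint, only day 14 of three days agrees. Day 7 cannot be supplied by a centre that follows Table 2; nor can day 1, on the assumption that the markers are drawn with the routine bloods. How many of the 1500 patients are affected depends on how many centres follow the table rather than the endpoint text, which the article does not show.

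For safety, the dosing day has no scheduled recording although the Harms section covers it under either starting point. Under-recording is possible, most plausibly in patients who react and do not proceed to surgery. Its size cannot be estimated from the document.

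The primary endpoint is not affected. The article does not show which laboratory schedule was intended, so neither the endpoint text nor the table can be declared the error.

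**What to change.** 1. **Inflammation endpoint.** Reconcile Efficacy assessment indicators with Table 2 so that endpoint days and draw days are the same, and state at which draws the inflammation markers are measured. There are two options. Aligning the endpoint to days 3, 5 and 14 needs no extra draw but may need added assays on those samples. Adding draws on days 1 and 7 keeps the endpoint as written but needs a new day 7 visit and two more draws. If data have already been collected, make the choice without looking at results by arm, and record the change and its date.

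2. **Safety rows.** In Table 2, tick both the adverse event row and the safety observation row in the preoperative 1-day column.

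3. **Start of recording.** In the Harms section, state once whether recording starts at consent or at first dose. If it is consent, tick the 2–3 day column as well.

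The cost is wording, one CRF page for the dosing day and possibly some marker assays. The visit and draws in item 1 arise only under its second option.
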